### Outcome measures

The primary outcome measure will be the proportion of patients experiencing a major bleeding event in the 90 days after hospital discharge. Major bleeding will be defined using the previously accepted definition of:

*"fatal bleeding, and/or symptomatic bleeding in a critical area or organ (especially intracranial or retroperitoneal), and/or bleeding causing a fall in haemoglobin level of 2 g/dL or more, or leading to transfusion of two or more units of whole blood or red cells" *[53].

Secondary outcome measures will be the combined incidence of major bleeding and thromboembolic events, death, cessation of warfarin therapy, INR control at 8 days post-discharge and unplanned hospital readmissions from any cause. INR control will be calculated based on the patient's individual target INR range, and defined as such as within this range ('therapeutic'), below the range ('subtherapeutic') or above the range ('supratherapeutic'). Rates of INRs greater than 4 will also be investigated as this confers a markedly increased risk of intracranial haemorrhage [54].

Other outcomes will include INR control to Day 90, QoL, warfarin knowledge, other adverse events (including minor bleeding) and adherence. Minor bleeding will be defined as bleeding requiring health professional consultation, but not hospitalisation, to ensure consistency and minimise the risk of recall bias. The EQ-5D utility score for QoL will be calculated using the United Kingdom Time Trade-Off data set, as has been reported previously [47]. No Australasian data set is currently available. Time in therapeutic INR range will be calculated using Rosendaal's linear interpolation method [55]. Warfarin drug interaction severity ratings will be classified as 'Severe', 'Moderate', 'Caution', 'Minor' and 'Nil' using the eMIMS database [56], while medical history will be based on the International Classification of Diseases 10 coding system (ICD-10) [57].

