### Sample size

Based on sample size calculations, groups comprising approximately 120 patients in each (control, 2-visit model, and 3-visit model) are estimated as being statistically adequate. This is based on the previous RCT of this model of care where 10% of the usual care group experienced a major bleeding event within 90 days post-discharge, which was reduced to 2% in the intervention group [36]. Using these figures, approximately 108 patients are needed per group at a power of 80% and p = 0.05. Published data are also available indicating that approximately 30-40% of patients commenced on warfarin experience a bleeding complication within 3 months [16,18,36,45]. The aim of the intervention program is to reduce this figure to below 10%, in which case approximately 72 patients are needed per group at a power of 80% and p = 0.05. The proposed recruitment targets are thus 160 in the control group and 240 in the intervention group (120 receiving the 2-visit model and 120 the 3-visit model).

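### The bleeding definitions leave admitted non-major bleeds in neither class, so major plus minor is not all bleeding and the any-bleeding aim has no matching outcome

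*Protocol article*

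**What the plan says.** All references are to the protocol article.

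- **Primary outcome.** The Outcome measures section fixes it as follows: "The primary outcome measure will be the proportion of patients experiencing a major bleeding event in the 90 days after hospital discharge". The criteria for a major bleed begin with death or site: "fatal bleeding, and/or symptomatic bleeding in a critical area or organ (especially intracranial or retroperitoneal". The remaining criteria concern blood loss: "bleeding causing a fall in haemoglobin level of 2 g/dL or more, or leading to transfusion of two or more units". Hospitalisation is not among the criteria.
- **Minor bleeding.** The same section states: "Minor bleeding will be defined as bleeding requiring health professional consultation, but not hospitalisation". The reason given is consistent counting and less recall bias. This outcome ranks below the primary and secondary ones, as the list of further outcomes shows: "Other outcomes will include INR control to Day 90, QoL, warfarin knowledge, other adverse events (including minor bleeding) and adherence".
- **Other places where a bleed is recorded.** Unplanned readmission from any cause is a secondary outcome. Under Control patients, AR-DRG codes and details from the notes are obtained for every readmission within 90 days, and the GP is asked to corroborate adverse events at about Day 90. Table 3 marks adverse events and readmissions at Visit 3 or Day 8, and again at Day 90.
- **Any bleeding (Sample size).** "approximately 30-40% of patients commenced on warfarin experience a bleeding complication within 3 months". The programme aims to bring this below 10%, for which about 72 patients per group are said to be needed. The same section gives 10% against 2% for major bleeding, with about 108 per group.

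**The concern.** The two bleeding classes should between them cover every bleed that the study means to count. They do not, because minor bleeding stops at the hospital door while major bleeding is defined by severity. The ordering that results is odd: a bleed settled by a consultation counts as bleeding, whereas one serious enough for admission but short of the major criteria does not.

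Two things are at stake. First, whether a bleed is admitted or handled in the community is partly a matter of care pathway. The service adds home visits and GP liaison, and readmission is itself an outcome that it hopes to influence. If the service kept some non-major bleeds out of hospital, they would enter the minor count in the intervention group while the same bleeds in the control group stayed outside it. Second, the Sample size section sets an aim for bleeding complications of any kind, and no listed outcome measures that.

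**Working it through.** **1. Cross the two definitions.**

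| | Not hospitalised | Hospitalised |
|---|---|---|
| Meets a major criterion | Major | Major |
| Meets no major criterion, consultation required | Minor | **Neither** |

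The lower right cell holds, for example, an admitted bleed at a non-critical site with a haemoglobin fall under 2 g/dL and fewer than two units transfused. The article gives no intermediate class for it.

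**2. Is the event recorded at all?** Yes. An unplanned admission counts as an all-cause readmission, its notes are obtained, and adverse events are collected in both groups. The information needed to classify it is therefore largely in hand.

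**3. Does the any-bleeding aim reach beyond major bleeding?** First, the plan's own figure. With p1 = 0.30, p2 = 0.10, mean 0.20, two-sided 0.05 and 80% power:

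- n = [1.960·√(2·0.20·0.80) + 0.842·√(0.30·0.70 + 0.10·0.90)]² / 0.20² = (1.109 + 0.461)² / 0.04 ≈ 61.6, that is 62.
- With continuity correction: (61.6/4)·[1 + √(1 + 4/(61.6·0.20))]² ≈ 71.2, that is 72.

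The stated 72 is reproduced, using the 30% end of the range. Nothing proposed here changes it, or the 108 for major bleeding.

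The usual-care rate for major bleeding in that section is 10%. If the two rates applied to the same patients, with each patient counted once in the worst class, non-major bleeding would be 30 − 10 = 20 to 40 − 10 = 30 points, or 20/30 = 67% to 30/40 = 75% of the any-bleeding rate. That is an assumption, since the cited sources cannot be seen. It does show that the aim cannot be assessed on major bleeding alone. Adding minor bleeding still omits the admitted non-major cell.

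**4. How does care pathway enter?** Let r be the true proportion with non-major bleeding, equal in both groups, and hC and hI the fractions of those bleeds admitted in control and intervention. Then:

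- recorded minor bleeding = r(1 − hC) in control and r(1 − hI) in intervention;
- spurious difference = r(hC − hI), which cannot exceed r·hC, the proportion of control patients with an admitted non-major bleed.

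If the service reduces admission (hI < hC), its minor-bleeding rate looks worse with no true difference. The article gives neither r nor h.

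**5. Illustration on assumed figures only.** Take a recorded control rate of 20% and the targets of 160 control and 240 intervention patients. A spurious excess of 2, 5 or 10 points would reach nominal two-sided significance with probability about 7%, 21% or 61%. For 5 points: pooled rate (160·0.20 + 240·0.25)/400 = 0.23; SE under the null √[0.23·0.77·(1/160 + 1/240)] = 0.0430; SE under the alternative √(0.16/160 + 0.1875/240) = 0.0422; z = (0.05 − 1.960·0.0430)/0.0422 = −0.81, giving 21%. By step 4, a 10-point excess would need at least 10% of controls to have an admitted non-major bleed, as many as the section expects to have a major one. The upper figure is therefore a limit for scale and not an expectation.

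**The case against.** The strongest reply is that little is lost. Minor bleeding is one item among the lower-ranked outcomes. The primary outcome, the combined bleeding and thromboembolic outcome and the readmission outcome are all intact. The larger group size rests on major bleeding. A condensed article may also leave event classes to a fuller document. Most of this stands and limits the weight of the point. It does not remove it, because the article does not leave the matter open: it states a definition with an express exclusion, and that exclusion makes the hole.

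A reader might infer more than the text supports, in three ways.

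- **That admitted non-major bleeds vanish from the safety comparison.** They do not. They count as readmissions and adverse events, with notes obtained. Only their classification as bleeding is missing.
- **That the service's own home visits serve as the qualifying consultation and inflate minor bleeding in the intervention group.** The definition says that the bleed must require the consultation. Visits scheduled by Table 4 take place whether or not there is a bleed, so a bleed merely mentioned there does not plainly qualify. Table 3 collects adverse events at Visit 3 or Day 8 and at Day 90 in both groups, and does not mark them at Visits 1 and 2. The wording could be more explicit, but a skew from this source is not shown. If it existed, it would count against the service.
- **That every bleed handled at a service visit should be excluded.** Some of these will have needed attention that a control patient would have sought from the GP. Excluding them could undercount intervention events and favour the service.

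**Conclusion.** The gap is certain from the wording: an admitted bleed that meets no major criterion belongs to neither class. Three consequences follow. Major plus minor is not total bleeding; the minor-bleeding comparison depends on care pathway; and the aim of moving any bleeding from 30-40% to below 10% has no matching outcome.

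The size of the gap cannot be derived, because the article gives no rate of admitted non-major bleeding. The figures in steps 4 and 5 of the working rest on stated assumptions and show only direction and scale. That the service shifts bleeds between hospital and community is plausible but not demonstrated. The primary and listed secondary outcomes are untouched. This is a definition worth correcting, with modest consequences, and not a threat to the main result.

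**What to change.** Replace the minor-bleeding definition and add one derived outcome:

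1. **Non-major bleeding:** any bleed that required consultation with a health professional or hospitalisation and does not meet the major definition. Report it split by hospitalised or not; the non-hospitalised part corresponds to the present minor class.
2. **Total bleeding to Day 90:** major plus non-major, listed among the other outcomes, as the measure that answers the any-bleeding aim in the Sample size section.
3. **One rule for both groups:** the bleed itself must have required the consultation. A bleed merely mentioned at a scheduled study or service visit does not qualify by itself; one that required professional attention does, wherever that attention was given.

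The readmission notes, adverse-event data and GP corroboration already planned supply what is needed. The cost is some reclassification from the readmission notes and one extra derived outcome. No new visits are needed, and the primary outcome and sample size do not change.

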### Statistical analysis

Demographic data will be utilised to compare the control and intervention groups for a range of parameters (e.g. age, gender, PhARIA class, living and medication management arrangements, co-morbidities, warfarin drug interactions) using independent samples t-testing for continuous data and chi-squared analysis for categorical data. Outcome data will be reported using parametric statistics, with independent samples t-testing utilised for the majority of continuous variables and chi-squared analysis for the majority of discrete variables. Data will be statistically analysed across the 3 groups (control, Level 1 Service, and Level 2 Service). For the evaluation questionnaires, responses will be recorded on modified Likert scales, with 0 representing "Strongly agree" and 10 "Strongly disagree". Qualitative feedback will obtained via open-ended questions. Data analysis will involve descriptive statistics and thematic analysis of the qualitative responses.

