### Control patients

Potential control patients will be approached prior to discharge and informed consent obtained for involvement in the study using standard Information Statements and Consent Forms. Informed consent will also be obtained from patients' GPs. Baseline data will then be collected during the patients' admissions and immediately after discharge.

After discharge from hospital, control patients will receive 'usual care' according to their community healthcare provider's usual practice. No restrictions will be based on usual care, except that it cannot involve a formal post-hospital outreach program as described in Table 2. Usual care will thus typically involve the patient undergoing venous blood sampling at their GP surgery or pathology specimen collection centre and the result being reported to the GP, who will then determine the need for dosage adjustments and communicate them back to the patient or carer. Alternative models of usual care may include the patient undergoing POC testing in the GP surgery and receiving immediate dosage adjustment advice during a GP consultation or from the practice nurse, in liaison with the GP; GPs or practice nurses utilising POC monitors during home visits; or mobile phlebotomy services offering venous sampling in the patient's home, with subsequent reporting of the result to the GP and communication of dosing instructions to the patient or carer.

In the control phase of the study, a single home visit for data collection purposes will be conducted by a project officer approximately 8 days post-discharge. At this visit, POC INR monitoring will be performed and data will be collected regarding the patients' warfarin therapy and INR results since discharge, medications and any adverse events.

Three questionnaires will be administered at this visit - the EQ-5D quality of life (QoL) questionnaire, which has been widely used across a number of clinical settings [46,47]; a previously validated warfarin knowledge questionnaire, the Oral Anticoagulation Knowledge (OAK) test [48]; and a modified Tool for Adherence Behaviour Screening (TABS) survey [49]. While TABS was developed in patients with chronic obstructive pulmonary disease, it was designed as a non-specific tool to screen for potential non-adherence in patients with chronic ailments and possesses advantages over other commonly used compliance measures in that it addresses both intentional and unintentional non-adherence and over- and under-utilisation.

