A final follow-up will be conducted via telephone and postal questionnaires (EQ-5D, the OAK test, TABS and the disease-specific Duke Anticoagulation Satisfaction Scale (DASS)) [50] approximately 90 days post-discharge. Corroboration of details of any adverse events experienced by the patient and their current medications and INR results will be requested from their GP at this time via a postal form. Non-responders will receive a reminder telephone call or fax after 4 to 8 weeks. For patients experiencing readmission to hospital during their 90 days post-discharge, Australian Refined Diagnosis Related Group (AR-DRG) codes and other details will be obtained from their notes from the relevant hospital's Medical Records Department. The data to be collected at each time point are summarised in Table 3.

**Table 3 T3:** Data collection summary

Data	Time point				
	
	Baseline	Visit 1	Visit 2*	Visit 3^i ^or Day 8^c^	Day 90
Demographics, alcohol intake, smoking history, drug history, height, weight, serum creatinine, haematocrit	✓				

Warfarin therapy details- indication, intended duration, target INR, newly commenced or continuing, heparin pre-treatment, inpatient doses/INRs, doses/INR on discharge, warfarin counselling documented	✓				

Medications, warfarin drug interactions	✓			✓	✓

Medical history	✓				

INR	✓	✓**	✓**	✓**	✓

Warfarin dosing/INR history	✓			✓	✓

Number of GP consultations (since discharge, or between Days 8 and 90)				✓	✓

Adverse events, hospital readmissions				✓	✓

Warfarin continuing, reason for discontinuation		✓	✓	✓	✓

Beyth Bleeding Risk score	✓^C^	✓^I^			

Warfarin dose, changes recommended, visit outcome, visit length, travel time		✓	✓	✓	

QoL (EQ-5D), warfarin knowledge		✓		✓	✓

QoL (Duke Anticoagulation Satisfaction Scale (DASS))					✓

Adherence (Tool for Adherence Behaviour Screening (TABS))				✓	✓

Self-reported health services utilisation					✓

(* Visit 2 if required, ** POC monitoring, ^C ^Control, ^I ^Intervention)

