## Discussion

The post-discharge period is well recognised as a high-risk time for patients taking warfarin [16,17,19-22,58,59]. POC INR testing has been suggested to have a number of advantages, including availability of the INR level at the same time as the consultation with a healthcare professional, improved compliance with warfarin as a result of the face-to-face interaction, increased convenience for the patient, more appropriate use of warfarin in rural and remote areas, and overcoming difficulties of frequent venepuncture [60]. There is also a strong focus on warfarin education as part of this intervention as studies have generally shown an inverse relationship between patient knowledge and adverse outcomes of warfarin therapy [61]. Patients' knowledge, drug compliance and anticoagulant control all improve after patient education becomes part of a structured management program [61-64].

The prospective, controlled cohort study design has been chosen in preference to a RCT as the focus of the program is on translation of the previous successful research program into practice, rather than solely demonstrating the benefits of the service. It is also believed that there is the strong possibility of a marked Hawthorne effect if the control and intervention phases were to occur simultaneously in the same hospital within a RCT, resulting in a possible modification of standard practice and a potential detriment to patient care. A multi-centred cluster RCT would require many more hospitals, time and expense, and would be likely to lead to difficulties in attracting collaborating hospitals and participants. Additionally, it was deemed impossible to blind participants to which phase of the trial in which they were involved.

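### The only outcome tests named are unadjusted, although the groups are not randomised and the service level is assigned by bleeding risk

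*Protocol article*

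**What the plan says.** The Discussion states the design: "The prospective, controlled cohort study design has been chosen in preference to a RCT". One reason given is an expected Hawthorne effect "if the control and intervention phases were to occur simultaneously in the same hospital within a RCT". The Control patients section also treats the control period as a phase of its own: "In the control phase of the study, a single home visit for data collection purposes will be conducted by a project officer".

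The primary outcome is binary. Under Outcome measures: "The primary outcome measure will be the proportion of patients experiencing a major bleeding event in the 90 days after hospital discharge".

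The Statistical analysis section gives baseline data one use: "Demographic data will be utilised to compare the control and intervention groups for a range of parameters", by t-test and chi-squared test. For outcomes it names "independent samples t-testing utilised for the majority of continuous variables and chi-squared analysis for the majority of discrete variables". It then sets the comparison groups: "Data will be statistically analysed across the 3 groups (control, Level 1 Service, and Level 2 Service".

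The Visit 1 text under Intervention patients explains how a patient reaches a level. Level 1 is open only to patients at low or intermediate risk on the Beyth index with no other risk factors. All others receive Level 2.

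No section names regression, stratification, matching, weighting, or a site or period term. Table 3 does collect likely confounders at baseline, among them "indication, intended duration, target INR, newly commenced or continuing".

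**The concern.** A crude chi-squared test or t-test estimates the effect of the service only if the groups would have had the same outcomes without it. Randomisation would give that in expectation; this design does not. Testing for baseline differences neither removes an imbalance nor shows that none exists.

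The article itself points to strong candidate confounders. Table 2 admits both newly started and continuing warfarin patients, and the Background says bleeding risk is highest early in therapy. The eight hospitals span PhARIA classes 1, 2 and 4. Intervention patients also depend on a completed HMR referral and an available trained pharmacist.

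The three-group analysis has a further problem that needs no assumption about recruitment. Level 1 and Level 2 are separated by predicted bleeding risk, and the primary outcome is bleeding. A crude difference between them, or between either one and an unselected control group, mixes selection with service.

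The results are meant to support national roll-out, so an effect estimate that cannot be separated from case mix matters.

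**Working it through.** **1. The plan's own figures.** The Sample size section uses 10% versus 2% major bleeding, a planned risk ratio of 0.02/0.10 = 0.20. Its 108 per group follows from n = [z_α√(2p̄(1−p̄)) + z_β√(p₁q₁+p₂q₂)]²/(p₁−p₂)², with p̄ = 0.06, one-sided 5% and 80% power: [1.645×0.3359 + 0.842×0.3311]²/0.0064 ≈ 108. (A two-sided 5% test gives 138; that is a separate matter.) The formula treats the groups as exchangeable and makes no allowance for confounding.

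**2. Control versus intervention, no service effect.** Assumed: 10% bleeding in controls (the planning rate), and a risk factor that multiplies risk by k = 3 and is present in 50% of controls. The factor of 3 and the prevalences are not in the document.
- Risk without the factor, b: b(0.5 + 0.5×3) = 0.10, so b = 0.05, and 0.15 with the factor.
- Intervention risk = b[(1−q) + 3q], where q is the prevalence in that group.

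| q | Intervention risk | Crude risk ratio |
|---|---|---|
| 40% | 0.05×1.8 = 0.09 | 0.90 |
| 30% | 0.05×1.6 = 0.08 | 0.80 |
| 60% | 0.05×2.2 = 0.11 | 1.10 |
| 70% | 0.05×2.4 = 0.12 | 1.20 |

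The last two rows show that the bias can run either way.

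**3. Effect on the test.** At the recruitment targets of 160 and 240, the rejection probability is Φ((d−1.96·se₀)/se₁) + Φ((−d−1.96·se₀)/se₁), where se₀ is the pooled and se₁ the unpooled standard error.
- 10% v 9%: se₀ = 0.0298, se₁ = 0.0301, total 6.5%.
- 10% v 8%: se₀ = 0.0289, se₁ = 0.0295, total 11%.

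The nominal level is 5%.

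**4. Whether the baseline test would catch it.** By the same formula for prevalences of 50% v 40%: pooled share (80+96)/400 = 0.44, se₀ = 0.0507, se₁ = 0.0506, and Φ((0.10−0.0993)/0.0506) ≈ 51%. A ten-point imbalance would go unflagged about half the time.

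**5. Level contrasts, no service effect.** Same risks (5% and 15%), with control at 10%.
- Complete separation (Level 1 all low-risk, Level 2 all high-risk): risk ratios versus control are 0.05/0.10 = 0.50 and 0.15/0.10 = 1.50. With 120 v 120, se₀ = 0.0387 and se₁ = 0.0382, so Level 1 v Level 2 rejects with probability Φ((0.10−0.0759)/0.0382) ≈ 74%.
- Partial separation (factor in 20% of Level 1 and 80% of Level 2): risks 0.05×1.4 = 0.07 and 0.05×2.6 = 0.13, so risk ratios are 0.70 and 1.30.

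**6. Information available for adjustment.** Expected events at the planning rates are 160×0.10 + 240×0.02 = 16 + 4.8 = 20.8, about 21. Over 8 sites that is 20.8/8 = 2.6 per site, and 4.8/8 = 0.6 per site among intervention patients. This is too few for strict stratification by site or a large outcome model.

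**The case against.** The strongest reply is that this is a condensed article. The tests are assigned to most variables, not all, and a full analysis plan that is not shown may contain an adjusted model. That stands as a limit: a reader might infer that no adjustment will be made, and the document does not establish that. But the article is not silent on method. It names the outcome tests and gives no other analysis for the primary outcome.

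Second, no imbalance has been demonstrated. A reader might infer that control and intervention patients differ in risk, or that sites are unevenly spread over the phases. The document gives no figures either way, and site-by-phase numbers are detail that an article may omit. Sequential timing is itself inferred from the references to phases; no recruitment dates are given.

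Third, the additional selection of intervention patients is partly controlled. Table 2 excludes from both groups anyone ineligible for an HMR or lacking a regular GP and community pharmacist, and GP consent is sought for controls too. What remains is completion of the referral and pharmacist availability.

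Fourth, the bias in the control versus intervention illustration is modest beside the planned risk ratio of 0.20. An imbalance of that size could not produce such an effect alone. A reader might reach for the tenfold contrast in the Background to claim a larger bias. It compares the first month of therapy with the period after the first year, whereas the outcome covers 90 days and continuing patients are not said to be beyond one year, so it does not fit.

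None of this answers the level contrasts, where the article's own assignment rule creates the difference in risk.

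**Conclusion.** The point holds in two parts of different strength. Crude contrasts of Level 1 with Level 2, or of either level with control, are confounded by design; their size depends on how strongly the assignment rule separates risk (risk ratios of 0.70 and 1.30, or 0.50 and 1.50, under the assumed values with no service effect). The crude control versus intervention contrast is exposed to case-mix and site-mix differences that the named tests cannot remove. Under the assumed threefold factor, a 10- or 20-point deficit in its prevalence among intervention patients gives a risk ratio of 0.90 or 0.80 and a true error rate of 6.5% or 11%. These are illustrations, not estimates of bias in this trial. The conclusion that the groups are in fact imbalanced, or that the result will be biased in the service's favour, goes beyond the document.

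**What to change.** Make the primary control versus intervention comparison an adjusted one, using propensity-score weighting or a penalised logistic model with few covariates fixed in advance. Candidates in Table 3 are new versus continuing warfarin, indication, age, creatinine, haematocrit and interacting drugs. A Beyth score can be added, but Table 3 records it at baseline for controls and at Visit 1 for intervention patients, so it should be computed from pre-discharge data in both groups. The article does not list the score's components, so it should be confirmed that they are all available before discharge.

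Enter site in the propensity model, as a coarse grouping, or as a penalised term. Apply the same adjustment to the other outcomes, including continuous ones, and report the crude t-tests and chi-squared tests as secondary.

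Present results by level descriptively, and state that neither Level 1 versus Level 2 nor either level versus control estimates an effect of visit number. State also that, if the phases are sequential, calendar period coincides with group and no covariate adjustment removes a period effect.

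The listed covariates are already collected. The cost is more analysis work and possibly a less precise estimate. Unmeasured confounding would remain.
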